### Sample size calculation

An objective of this study is to assess the feasibility of recruiting and retaining the required number of participants per nursing home which would be needed in a definitive RCT. Therefore, the sample size calculation for this pilot feasibility study is based on the estimated power calculation for a definitive cluster RCT using the primary outcome measure, the Timed Up and Go (TUG) test [23]. In the absence of normative TUG data for an Irish cohort of older adults living in nursing homes, sample size calculations for a definitive RCT were estimated using a New Zealand sample of older adults living in residential care [12]. The sample size requirements for a definitive RCT were calculated as being a minimum of four clusters of size 20 in each arm, in order to have 80% power (α = 0.05) to detect a mean change in TUG score of 4.7 s (± 6.8 s). The current study will recruit one nursing home for each arm. The desired number of participants in each nursing home will be maintained as 20 in order to assess the recruitment potential, recruitment time and feasibility of delivering the intervention to this number of participants. The number of participants lost to follow-up per nursing home will be recorded to inform the final numbers needed when recruiting to the definitive RCT.

### Recruitment

#### Recruitment of nursing homes

The Directory of Nursing Homes [24] is a comprehensive listing of all public and private nursing homes in Ireland and will be used to identify all potentially eligible nursing homes in County Galway. The reason for non-eligibility of nursing homes from this list will be documented. All eligible nursing homes will be posted an invitation letter along with a booklet containing information about the study. This will be promptly followed up with a telephone call, where the researcher will attempt to speak directly with the Director of Nursing (DON) or another person in charge. The nursing home will be provided with two weeks to consider participation. At this point, if the nursing homes would like to further explore participation in the study, a meeting will be convened between the researcher and DON. The equal likelihood of being in the intervention or control arm of the study will be clearly explained to all nursing homes from the outset. A list of nursing homes willing to participate will then be created. From this list, one nursing home will be randomly selected, by a statistician independent of this study, to receive the intervention and a second will be randomly chosen for the control. The group allocation will be concealed from potential participants, the nursing home and the researchers involved in recruitment and assessment in a sealed opaque envelope until all participants have been recruited to the study and have completed baseline assessment.

#### Recruitment of participants

The DON in each nursing home or her nominee will identify all residents who satisfy the eligibility criteria. The main reasons for residents not meeting these eligibility criteria will be documented, as this will provide useful feasibility data. General practitioner (GP) clearance will be sought for each potential participant before they are invited to participate. Once this screening is complete, a member of staff will ask potential participants if they would be willing to talk to a researcher about participating in a PA research study. Once a potential participant agrees, the staff member will introduce the researcher to the potential participant. The researcher will explain the study in simple terms and explore whether the resident is interested in participating. In the case of the resident expressing a disinterest in the study, no further actions will be pursued and the reason for their lack of interest will be documented. If interested, the resident will be provided with an information leaflet. This document will be reviewed verbally with the participant in order to overcome any potential literacy difficulties and large font sizes will be used. The information sheet will clearly inform participants of the purpose, process, potential benefits and harms of the study, data collection procedures, time commitment, its voluntary nature, as well as providing an assurance of confidentiality. The equal likelihood of receiving the intervention or control arm of the study will be clearly explained to all participants, as well as their freedom to withdraw from the study at any stage without any consequence to their care.

Where a participant expresses an understanding of the study, its voluntary nature and a choice to participate, the researcher will finalise the consent process directly with the person. In instances where it is not possible for the potential participant to provide written informed consent, assent will be obtained from the participant. In line with current evidence [25], assent will be obtained from the participant by an affirmative agreement to participate as expressed verbally (i.e. orally) or a non-verbal indication of willingness to cooperate with study procedures, i.e. behaviourally (e.g. acting agreeably) or emotionally (e.g. having a positive facial expression). In addition to assent, the person’s next of kin will be asked to provide written informed consent on behalf of their relative. The next of kin will be asked to make their decision on the basis of their knowledge of the person’s wishes, attitudes and values. Assent will be assessed continually throughout the study for all participants.

### Intervention

Key elements of SCT have been incorporated into the PA intervention, using the strategies outlined in Table 3. The PA intervention will comprise three components led by a researcher who is a qualified physiotherapist.Participant goal-setting

**Table 3 Tab3:** Specific intervention strategies and how they relate to each theoretical construct [18]

Behaviour change principle	Intervention strategies
Knowledge	- Researcher will educate each participant on health benefits of PA in the context of their own health - Educational posters displayed in nursing home - Re-enforcement by the care staff monitoring the intervention
Self-efficacy	- Completion of baseline physical assessments - Involvement of participants in refining their personal PA programme - Mastery of PA programme throughout intervention - Observation of other participants being physically active - Encouragement and constructive feedback from researcher and staff
Outcome expectations	- Discussion of outcome expectations in initial meeting between researcher and participant - Self-monitoring of PA programme via logbook - Reassessment of goals at follow-up to chart improvement
Goal-setting	- Participant sets PA related goals and performance indicators - Goals and PA programme displayed on bedroom wall - Reassessment of goal attainment at follow-up
Perceived impediments and facilitators	- Barriers and facilitators to goal attainment discussed and addressed in initial meeting - Allocation of staff to monitor intervention and support participants with their PA programmes - Reflection on personal diary - Participants encouraged to carry out walking together for social support

The researcher will meet with each participant individually to educate them of the benefits of PA in their own context and to facilitate participants in setting a small number of activity-based goals that they would like to achieve over the intervention period. Goals should be in relation to performing a physical task, such as walking to the dining area for meals, participating in particular group activities or gardening. The Bangor Goal Setting Interview [26] will provide a structured format for the goal-setting process. First, the researcher will facilitate the participant to explore different domains of daily life and identify issues of importance to them that may form the basis of goals. The importance for change and readiness to change in each of these areas will be explored using the principles of motivational interviewing. The researcher will facilitate the participant in revisiting each area and choosing the desired goals using SMART (specific, measurable, achievable, realistic and timely) criteria. The researcher and participant will work together to set goal attainment indicators, which will provide clear descriptors of what would constitute 25%, 50% and 75% goal attainment [26]. Finally, the participant will be asked to rate their current performance and satisfaction with performance on a Likert scale of 1–10 (where 1 means cannot do or am not doing successfully and 10 means can do and am doing very successfully). A visual representation of this scale will be used to assist participants. A separate, independent rating of goal attainment will be recorded by the researcher following observation. Barriers and facilitators to achieving the goal will be discussed with an emphasis on resources that will help in overcoming obstacles and achieving their goals.b)PA programme

Using the information gathered from the baseline assessment and goal-setting exercise, a PA programme will be developed by the researcher and tailored to each participant. The participant will be given an opportunity to refine the PA programme with the researcher before it is finalised, as participant satisfaction with PA interventions is important for adherence [27]. PA programmes will be carried out on three days per week. Integral to each PA programme will be a walking component (i.e. structured and gradual increases in daily walking time) and sit-to-stand exercises (i.e. a specified number of repeated rises from a chair). These are functional and accessible means of providing the aerobic and resistance components considered as important to PA programmes [28]. Opportunities for walking will be identified with each participant and the care staff. This will be based on lengthening walks that the participant is already undergoing. For example, the participants’ walk to or from the dining area or their walk from the bedroom to the seating area will be increased by 1–5 min initially and progressed to a maximum of 10 min. Where possible, participants will be encouraged to walk with others, as exercising with peers has been shown to enhance adherence to and persistence with an exercise program among older adults [29]. Sit-to-stand exercises will be embedded into the participant’s daily routines, for example rather than rising from a chair once, participants will complete a series of sit-to-stands in their bedroom, the dining room or the seating area. Depending on individual ability, this will begin as two sets of 2–5 repetitions initially and progressed to a maximum of three sets of 15 repetitions. The remaining components of the PA programme will be tailored around each participant’s specific functional goals and will be based on repeating particular functional and meaningful activities. The researcher will progress each PA programme as tolerated by each participant. All participants in the intervention group will commence the PA programme at the same time.

A poster displaying the participant’s goals and PA programme will be visible on the wall in their bedroom to promote adherence. Where possible, participants will be encouraged to document their own adherence to their PA programme using an easy-to-complete diary provided by the researcher, detailing the time spent walking and the number of repetitions achieved for each activity. Where cognitive or physical barriers prevent participants from completing their own adherence diary, the staff will be responsible for completing the diary for them. When the PA occurs upon the participant getting up in the morning, the staff member assisting the participant in getting up will be responsible for completing the adherence diary. For daytime PA, the staff member who supervises the PA will document adherence on a centrally placed progress board. Space will be provided to detail any deviations or modifications of the PA programme. Recording adherence to PA on a daily basis like this provides the most detailed data [30] and is less susceptible to recall errors which are evident in many retrospective PA questionnaires [31].c)Staff training and support

All nursing home staff will be invited to attend two education sessions. The first session will take place at the beginning of the intervention and the second at the midway point. Table 4 outlines the content of these educational sessions. Staff will be responsible for overseeing the completion of the participant’s PA programmes which may involve providing reminders, encouragement or assistance with PA programmes and assistance with documenting adherence. The researcher will support the nursing home staff to supervise the participants PA programmes through twice weekly support visits and ongoing telephone support. Posters will be displayed on the nursing home notice boards to highlight the impact of PA on health and wellbeing and to generate awareness of the study among nursing home staff, residents and visitors.

**Table 4 Tab4:** Content of two staff education sessions

Session 1 (2 h)	
(i) Welcome, introduction and the importance of PA for older adults	
(ii) What the intervention aims to achieve and the rationale for the intervention	
(iii) Overview of the goals set by participants	
(iv) Implementation plan, including the structure on supervising participants with their programmes, completing the adherence sheets and addressing potential barriers to implementation	
(v) Techniques for educating participants on the benefits of PA and motivating participants with their programmes	
(vi) Questions and answers	
Session 2 (1 h)	
(i) Evaluation on progress of the study	
(ii) Addressing issues which may be challenging the implementation of the programme	
(iii) Methods to assist participants’ continued engagement with their programme	

### Control group

The participants in the control group will receive usual care, which will be guided by current nursing and medical care plans. Participants in the control group are not restricted in any way regarding their PA behaviour. However, participants will be asked to document any changes in PA which occurs during the intervention period and the researcher will verify this with the key nurse at each follow-up. The feasibility and time taken to collect this information will be documented. At the end of the intervention, if a positive outcome is indicated, the nursing home staff which takes part in the control arm will be provided with the materials used in the intervention arm. The researcher will also deliver an educational session and guidance on how to deliver the programme in their nursing home.

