**Secondary research questions**	
What are the preliminary clinical outcomes and cost-effectiveness of the intervention compared to the control group? • What are the estimated outcomes of the intervention in comparison with the control group and are these sustained at 12-month follow-up? • What are the costs of the intervention in comparison to costs in the control group?	

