#### Outcome measurements

Quantitative outcome data will be collected in an unblinded manner from participants at T1 (baseline, pre-intervention), T2 (directly after completion of the intervention at three months) to examine the immediate intervention outcomes and T3 (12 months following the start of the intervention) to examine if the outcomes are sustained beyond intervention completion.

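### If the three-month result is judged positive, control-home staff receive the programme materials and training up to nine months before the 12-month comparison with usual care

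*Protocol article*

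**What the plan says.** The Control group section defines the comparator as usual care and then adds a hand-over, which opens: "At the end of the intervention, if a positive outcome is indicated, the nursing home staff which takes part in the control arm". Those staff are to get the intervention arm's materials. The section goes on: "The researcher will also deliver an educational session and guidance on how to deliver the programme in their nursing home". It does not say what counts as a positive outcome. It asks control participants to note changes in physical activity over the intervention period, with the key nurse confirming this information at each follow-up.

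The Outcome measurements section fixes the calendar. The second assessment is "T2 (directly after completion of the intervention at three months", and the third is "T3 (12 months following the start of the intervention) to examine if the outcomes are sustained beyond intervention completion".

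The secondary research questions in Table 1 ask: "What are the estimated outcomes of the intervention in comparison with the control group and are these sustained at 12-month follow-up". The Health economic analysis section collects resource use (three-month recall) and EQ-5D in both groups at baseline, three and 12 months. Table 5, criterion 4, grades participant retention at 12 months in both groups.

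The Intervention section describes the full package: "The PA intervention will comprise three components led by a researcher who is a qualified physiotherapist". These are individual goal-setting, a tailored programme that the researcher progresses, and staff training and support. The last includes two education sessions and "twice weekly support visits and ongoing telephone support".

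**The concern.** The 12-month question is whether any benefit lasts relative to a home under usual care. The hand-over is meant to enable control-home staff to run the programme, and it is timed before that comparison. The Design and setting section randomises whole homes to prevent contamination between groups, yet this rule allows contamination by design.

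The rule is also selective. It operates only when the three-month result looks good, which is when the sustained-effect question is of most interest. If control residents then become more active, the 12-month gap between homes narrows for a reason unrelated to whether the intervention home kept its gains.

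The same applies to the 12-month cost and EQ-5D data and to control retention at 12 months. Retention feeds a progression criterion, and Table 1 lists attrition by group under a primary research question.

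**Working it through.** The plan gives no figure for this point, so there is none to reproduce. The check is mainly of timing and content.

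1. **Timing.** Intervention completed at month 3; T3 at month 12 (Outcome measurements). Longest interval from hand-over to T3: 12 − 3 = 9 months, or 9/12 = 75% of follow-up. This is a maximum interval after an offer, not measured exposure. No section defers the hand-over until after T3.

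2. **What is measured after the hand-over.**
   - TUG and the other between-home outcomes at T3.
   - Resource use: the 12-month form looks back three months, so it covers months 9 to 12, all after a month-3 hand-over.
   - EQ-5D: if QALYs are computed by the trapezoid rule (an assumption; the article names no method), the 12-month weight is (9/12)/2 = 0.375, the three-month weight (3/12)/2 + (9/12)/2 = 0.50, and the baseline weight (3/12)/2 = 0.125. So 37.5% of the QALY weight rests on the post-hand-over measurement.
   - Control retention at 12 months (Table 5, criterion 4).

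3. **What is handed over.** Materials, one session and guidance, all to staff. The researcher-led goal-setting, the researcher's tailoring and progression of each programme, and the regular support visits are not included.

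4. **How often the condition might be met.** This depends on the undefined term. Inputs: 20 participants per home; effect 4.7 s and ± 6.8 s read as an SD (Sample size calculation); intracluster correlation assumed 0 to 0.10, since none is given. SE = 6.8 × √[(2/20) × (1 + 19 × ICC)].

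| ICC (assumed) | SE (s) | P(observed difference favourable), Φ(4.7/SE) | P(favourable and significant), Φ(4.7/SE − 1.96) |
|---|---|---|---|
| 0 | 2.15 | 0.986 | 0.589 |
| 0.05 | 3.00 | 0.941 | 0.346 |
| 0.10 | 3.66 | 0.900 | 0.249 |

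   With no true effect, a favourable difference occurs with probability 0.50. The last column is idealised, because one home per arm gives no estimate of between-home variation. Depending on the definition, the hand-over could be close to certain or fairly uncommon when the effect is real.

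5. **Size of any dilution.** If a 4.7 s effect persisted to month 12 and the control home reproduced a fraction f of it, the contrast would be 4.7 × (1 − f): 4.7 s at f = 0, 2.35 s at f = 0.5, and 0 at f = 1. Persistence and f are both assumptions. The documents do not narrow this range, so it is an illustration and not an estimate.

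6. **Whether uptake would be seen.** Control participants' activity changes are requested for the intervention period, months 0 to 3. The key nurse's check concerns that same information. Programme use in months 3 to 12 is not named.

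**The case against.** A reader might infer that the control home is simply given the intervention for 75% of follow-up, that the usual-care comparator is lost, and that a true lasting effect would look as if it had faded. The documents do not support that reading. The hand-over is conditional; if the condition is not met, the comparator is intact. The package goes to staff and lacks the researcher-led elements, and no control resident is assigned a programme. Nine months is the longest possible interval and would require immediate and continued delivery to become exposure. The course from T2 to T3 within the intervention home is unaffected, and the abstract plans within-individual as well as between-group estimates. The three-month outcome and cost data are also untouched. For retention, neither the direction nor the size of any distortion can be derived.

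The case for a low weight is also fair. The sustained-effect and cost questions are secondary. The Quantitative analysis section calls all outcome analyses preliminary. With one home per arm, the 12-month contrast is already confounded with the home itself. The unblinded look at three-month data threatens no error rate, since the article describes no confirmatory test and acknowledges the lack of blinding. The article condenses a fuller protocol that may define a positive outcome.

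All of this limits severity. It does not remove the conflict: the article itself schedules the hand-over before T3 and describes the control as usual care. Cautious interpretation cannot restore that comparator if the home has begun the programme, least of all if uptake was not recorded.

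**Conclusion.** The point holds in conditional form. If the three-month result is judged positive, control-home staff are equipped to run the programme up to nine months before T3. The 12-month between-home outcome comparison, the 12-month resource-use and EQ-5D data, and 12-month control retention may then depart from usual care by an amount the documents do not allow one to estimate. Any departure would arise selectively after a favourable early result.

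This rests on reading the end of the intervention as month 3, which the Outcome measurements section states directly. It is a moderate issue and does not have to be fixed before the pilot can answer its main feasibility questions. It is still worth correcting, because the rule weakens the 12-month data in the scenario where they would be most used.

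**What to change.** Change the Control group section so that the materials, educational session and guidance are offered to the control home after its last 12-month (T3) assessment, with no trigger based on three-month data. The offer can be unconditional or can rest on the final results.

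If an earlier hand-over has already been agreed with the home, keep to it, but record the home's uptake of the programme through month 12 and do not describe the 12-month contrast as one against usual care.

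The text change is small. The real cost is that the control home waits up to nine months longer. Because the Trial status section puts recruitment at March to June 2018, its agreement may also need updating.
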